## Abstract

**Background:**

Blood pressure (BP) lowering in people who have had a stroke or transient ischaemic attack (TIA) leads to reduced risk of further stroke. However, it is not clear what the target BP should be, since intensification of therapy may lead to additional adverse effects. PAST BP will determine whether more intensive BP targets can be achieved in a primary care setting, and whether more intensive therapy is associated with adverse effects on quality of life.

**Methods/Design:**

This is a randomised controlled trial (RCT) in patients with a past history of stroke or TIA. Patients will be randomised to two groups and will either have their blood pressure (BP) lowered intensively to a target of 130 mmHg systolic, (or by 10 mmHg if the baseline systolic pressure is between 125 and 140 mmHg) compared to a standard group where the BP will be reduced to a target of 140 mmHg systolic. Patients will be managed by their practice at 1-3 month intervals depending on level of BP and followed-up by the research team at six monthly intervals for 12 months.

610 patients will be recruited from approximately 50 general practices. The following exclusion criteria will be applied: systolic BP <125 mmHg at baseline, 3 or more anti-hypertensive agents, orthostatic hypotension, diabetes mellitus with microalbuminuria or other condition requiring a lower treatment target or terminal illness.

The primary outcome will be change in systolic BP over twelve months. Secondary outcomes include quality of life, adverse events and cardiovascular events.

In-depth interviews with 30 patients and 20 health care practitioners will be undertaken to investigate patient and healthcare professionals understanding and views of BP management.

**Discussion:**

The results of this trial will inform whether intensive blood pressure targets can be achieved in people who have had a stroke or TIA in primary care, and help determine whether or not further research is required before recommending such targets for this population.

**Trial Registration:**

ISRCTN29062286

## Background

Stroke is the third largest cause of death in England, and the single largest cause of adult disability[1]. A National Audit Office report (2005) highlighted the high cost of stroke to the NHS: about £2.8 billion per year in direct care costs, and an additional £1.8 billion per year cost to the wider economy due to lost productivity and disability [2]. Recent estimates suggest that between 30-45% of strokes are recurrent events, [3] so more effective secondary prevention could result in significant savings: the National Audit Office estimates that preventing just 2% of strokes in England in a year could save care costs of over £37 million [2]. NICE has identified better control of hypertension as one of the interventions that are cost saving for the NHS [4].

The PROGRESS trial demonstrated that blood pressure lowering is beneficial in reducing risk of stroke amongst both hypertensive and non-hypertensive individuals with a history of stroke or TIA recruited in secondary care immediately after their cerebrovascular event. In this trial, patients were randomised to either a combination of an ACE inhibitor and thiazide diuretic against double placebo, or an ACE inhibitor alone against single placebo. The decision to randomise to one or two agents was made by the supervising physician on the basis of whether or not they thought it was safe to randomise an individual patient to two agents. Mean blood pressure in the intervention arm was reduced from 147 mmHg systolic by 9 mmHg (SE 0.3), and this was associated with a 28% reduction in stroke risk [5]. The positive result of the PROGRESS trial raises a supplementary question: by how much should blood pressure be lowered? No randomised trials have specifically compared different target blood pressures (BP) in the post-stroke/TIA population. Observational data (although not collected specifically in people with a history of stroke or TIA) suggest that the lower the blood pressure, the lower the risk of vascular mortality, at least down to 115 mmHg systolic [6,7]. There is some evidence from PROGRESS to support this, in that the sub-group of patients whose baseline BP was between 120 and 140 mmHg who were randomised to combination therapy had a significantly reduced risk of stroke compared with control, though this benefit was not observed in patients who were randomised to a single agent [8]. Guidelines have tended to interpret this evidence by recommending a target of 130 mmHg for systolic blood pressure in people with cerebrovascular disease [9,10]. However, the question remains whether such a target is prudent in general (42% were randomised to a single agent and gained no benefit) and whether it is achievable in primary care (PROGRESS was secondary care based) [5].

Long term management of blood pressure following stroke and TIA is predominantly carried out in primary care. Recent studies of blood pressure control in this setting paint a mixed picture of implementation of guidelines. In a study of seven general practices in South Birmingham in 2002, 63% of patients with a previous stroke or TIA had BP above the 140 mmHg target, and 80% above the 130 mmHg target [11]. 68% of these patients were prescribed BP lowering therapy. An analysis of general practice data on the QRESEARCH database for 2002-2004 found that of all patients with incident stroke, blood pressure was not recorded in 25% of patients, and where it was recorded, it was above the 140 mmHg target in 47% [12]. An analysis of the impact of the Quality Outcomes Framework (QOF) carried out for the National Audit Office found that the proportion of people with a history of stroke or TIA who had their BP measured in the preceding 15 months rose from 89% to 95% between 2004 and 2005, and the proportion with a BP below 150 mmHg (the target level for the QOF) rose from 69% to 80% suggesting some improvement [13]. An analysis of the care of over three thousand patients who had a TIA during 2004-5 found that 60% had a BP equal to or below the 140 mmHg target, though only 50% were on any blood pressure lowering therapy [14].

In summary, although there is some evidence that blood pressure lowering in people who have had a stroke or TIA is beneficial, there is no clear guidance on what the target BP should be. Furthermore, data collected from primary care suggest that guidelines from the British Hypertension Society and Intercollegiate Stroke Working Party are not being fully implemented. This research is designed to support implementation of the guidelines by both addressing the gaps in the underlying evidence base, and testing a specific mechanism for implementation of blood pressure lowering.

## Methods/Design

### Study aims

The primary aim of Past BP is to determine whether a more intensive target BP for people with stroke or TIA in a pragmatic primary care setting will lead to a lower BP.

Secondary aims of the research are to:

• determine the impact of a more intensive BP target on patient quality of life;

• identify the barriers to implementation of more intensive blood pressure lowering;

• to explore whether the potential benefits associated with intensive blood pressure lowering might be outweighed by potential adverse effects on quality of life and costs.

The latter point will be explored by economic modelling. If there is uncertainty as to whether there is net benefit from intensive blood pressure lowering, then there would be a case for a trial of different targets for BP lowering in primary care that is powered to detect differences in clinical end-points.

The study will also investigate patients' understanding and beliefs about the relationship between blood pressure and stroke, and patients and healthcare professionals experience of participating in the study, which may contribute to the success or otherwise of the intervention.

### Study design and setting

Past BP is a primary care based pragmatic randomised controlled trial (RCT) in which people with stroke or TIA are randomised to an intensive blood pressure (BP) target group (target 130 mmHg systolic, or 10 mmHg reduction in systolic BP if baseline BP 125 - 140 mmHg) or a standard BP target group (target 140 mmHg systolic).

We will also use qualitative methodologies to investigate patient and healthcare professionals understanding and views of BP management. Grounded theory methods will guide sampling, data collection and data analysis [15,16]. Sampling will be done purposively to allow for the maximum variety of characteristics. Semi-structured interviews will be carried out [17] and will continue until new concepts are no longer being generated and theoretical saturation is reached.

#### Ethical Considerations

Full ethical approval for this study has been obtained from Warwickshire Research Ethics Committee, reference 08/H1211/121. A Data Monitoring Committee and a Trial Steering Committee will monitor the progress of the RCT.

### Randomised controlled trial

#### Study Interventions

Management of both treatment groups will follow study specific treatment protocols that reflect the current NICE guidelines [18]. However, the thresholds for intervention between the two treatment groups are different: all patients in the intensive target arm will have their BP lowering therapy intensified at trial entry since the target will be automatically below their baseline BP whereas only those patients in the standard arm whose BP is above 140/90 mmHg will have their therapy intensified at the outset.

#### Identification of eligible patients

Eligible patients will be identified from general practices from the Central England Primary Care Research Network and from the Midlands Research Practice Consortium (MidReC). Each practice will run a search of their clinical computer system to identify all patients on the stroke/TIA register. Where possible, the computer search will exclude patients with clear exclusion criteria (see table 1). The GP will also remove patients for whom a study invitation would be inappropriate (for example, those with a terminal illness). Patients with no clear exclusion criteria at this stage will be sent a letter inviting them to attend a study baseline clinic appointment.

**Table 1 T1:** Study inclusion and exclusion criteria

*Inclusion criteria*
On practice TIA/stroke register

***Exclusion criteria***

Systolic BP < 125 mmHg at baseline;
Already taking 3 or more anti-hypertensive agents; orthostatic hypotension (>20 mmHg postural change in systolic BP after 1 minute standing)
Patient already has a treatment target of 130 mmHg systolic BP specified
Unable to provide informed consent.
Insufficient corroborative evidence of stroke/TIA from medical record and patient interview

#### Baseline clinic appointment

This clinic appointment is carried out by a Research Nurse. At this appointment the nurse will: confirm the stroke/TIA diagnosis through review of medical records and patient interview; determine whether there are any exclusion criteria present; and collect baseline data (see table 2). If the patient is eligible and willing to take part, the nurse will also gain written informed consent prior to randomisation, and will telephone the randomisation service to obtain treatment group allocation.

**Table 2 T2:** Timing and content of study assessments.

*Baseline data: research nurse administered*
*Socio-demographic characteristics:*
Age; Ethnicity; Gender; Postcode

*Validation of stroke/transient ischaemic attack:*
Review of medical records with patient history

*Clinical measures:*
Six blood pressure (BP) measurements, calculating mean of 2^nd ^and 3^rd ^measurements and recording details of: arm used; arm circumference; BP cuff size; and time BP measurement started
24 hour ambulatory BP recording

*Medical history*
Previous history of angina, myocardial infarction, heart failure, atrial fibrillation, CABG/angioplasty (balloon)/or stent, peripheral vascular disease, diabetes, chronic kidney disease. Current prescription medications. Smoking status and alcohol intake

*Patient questionnaires - self-completion*
Health related quality of life assessed by the SF-36 [20] and EQ-5 D [19]
Disability assessed by the Modified Rankin Scale [26]
Medication Adherence Report Schedule (MARS) for BP treatment [27]
Symptoms/side effects questionnaire

*Patient questionnaire - research nurse completion*
Cognitive function assessed by the Mini Mental State [21]

*Eligibility and consent*
Review inclusion and exclusion criteria and record outcome of consent process

***Patient follow up for BP control***

*GP appointment at any time patient BP medication review required*
Action taken to treat/monitor side effects
Action taken to treat BP above target using study algorithm (see figure 1)
Make appointment with practice nurse at appropriate interval (see figure 2)

*Practice nurse follow up - 1-3 month intervals*
Six BP readings, as per baseline data collection
Side effects of BP medication
Refer patient to GP or make further appointment with practice nurse (see figure 2)

***Patient follow up by research team***

*Research nurse follow up - 6 and 12 months post randomisation*
Six BP readings, as per baseline data collection
24 hour ambulatory BP recording (12 month f/u only)
Check details of patient visits to GP and practice nurse
Diagnosis of key medical conditions (as per baseline data collection) since baseline or the previous research nurse follow up
All hospital admissions or outpatient visits since baseline or the previous research nurse follow up
Record of medications introduced since baseline or the previous research nurse follow up
Monitor compliance with repeat medication since baseline or previous research nurse follow up
Completion of patient questionnaires, as per baseline data collection.

*Obtaining information on patients who died*
Records flagged at NHS central register

Once the treatment allocation has been obtained, patients in the intensive target group and any patients who have been randomised to the standard treatment group whose BP is above the target of 140 mmHg will see a GP in order to have their treatment intensified using the study specific treatment protocol (see figure 1). Patients in the standard group whose BP is below target will receive an appointment to see the practice nurse three months post randomisation.

**Figure 1 F1:**
[figure not shown]
**Summary of Algorithm for BP control**.

#### Randomisation

The randomisation will use minimisation to balance the randomised groups on the basis of age (<80, ≥80), sex, diabetes mellitus, atrial fibrillation (because of the difficulties of obtaining accurate BP measurements in this group), baseline systolic BP and practice.

#### Patient follow-up procedures

Patients will be followed up from trial entry for 12 months. Follow up will be carried out in several ways. Firstly, practice nurses (PNs) will see patients at 1-3 monthly intervals, depending on BP and treatment allocation. (see figure 2) The PN will take a patient's BP and refer them to the GP if the BP is above target, or if the patient is having problems with adverse effects to their BP medication. The GP will then adjust the medication, following the study treatment protocol (see figures 1). At 6 and 12 months patients will be followed up by a research nurse (RN) where details of primary and secondary outcomes will be collected. (see table 2). Finally, the records of patients will be flagged at the NHS Central Register.

**Figure 2 F2:**
[figure not shown]
**follow up procedure**.

#### Patient outcome measures

The primary outcome measure is a change in systolic blood pressure between baseline and 12 months. Blood pressure measurements are performed in a standardised way, using BHS validated automated electronic monitors supplied and validated for the study. The patient will be seated for 5 minutes and then 6 measurements will be taken at minute intervals. The second and third measurements are averaged to give the reading. As the intensive target group have their BP monitored more frequently than those in the standard group, there may be some diminution of the 'white coat' effect in this group; the mean of readings 2 to 6 and the mean of 5 and 6 will be used to monitor for this. Any differences between the groups in the primary outcome should be sustained in the mean of the 5^th ^and 6^th ^readings (by which time any accommodation effect is likely to have worn off), enabling us to determine whether accommodation has a significant effect in this study. 24 hour blood pressure recordings using an ambulatory sphygmomanometer will be recorded at baseline and at twelve months. 24 hour ambulatory measurement will be unaffected by accommodation, so will provide further evidence as to whether or not this was significant in this study.

A variety of secondary outcome measures are also assessed during the RN follow up appointments. (see table 2) Key secondary outcomes are: additional measures of BP (change in diastolic and mean daytime ambulatory systolic BP between baseline and twelve months); measures of adherence (including GP adherence to protocol and patient adherence to prescribed medication); quality of life (EQ5 D [19]; SF36 [20]); side effects, tolerability and adverse events; clinical outcomes (including major cardiovascular events [composite of fatal and non-fatal stroke, myocardial infarction or fatal coronary heart disease and other cardiovascular death], all cause mortality, cognitive function [21] and hospital admissions). Key secondary events (stroke; myocardial infarction; fatal coronary heart disease and other cardiovascular death) will be reviewed by independent clinicians blinded to treatment to ensure unbiased coding of these events.

#### Sample size

Randomisation of 610 patients (305 per arm), with 12 months of follow-up, will detect a 5 mmHg difference in systolic BP between groups with 90% power and at a significance level of 5% assuming a standard deviation of 17.5 mmHg (a conservative estimate of standard deviation falling between 16, a figure derived from the same sort of patients as included in this study [11] and 19, the standard deviation in the PROGRESS Study [5]). The calculation assumes that: a 5 mmHg difference in systolic BP is of clinical significance, leading to a 20% reduction in major vascular events;[22] that there will be 5% mortality at six months, and a further 10% of patients will not have their BP measured at six months.

With regard to ambulatory blood pressure measurement, one of the secondary outcomes of the study, randomisation of 450 patients (225 per arm) will detect a 4 mmHg difference in systolic BP between groups with 90% power and at a significance level of 5% assuming a standard deviation of 11.7 mmHg [23]. This calculation assumes that 80% of patients will have ambulatory blood pressure measured at 12 months.

To recruit patients from primary care, an estimate of the number of practices is required. Approximately 50 practices with an average list size of 7,500 will be needed in order to recruit the required number of patients. This will generate 5,625 patients on practice TIA/stroke registers (from the QOF data, the overall prevalence of TIA/stroke in primary care is 1.5%). From our analysis of South Birmingham data [11], we anticipate that 13% of these patients will be ineligible because they are already on three or more anti-hypertensives, and 28% because they will not fulfil the diagnostic criteria for a history of stroke or TIA for the study [24]. We assume that 30% of patients will respond to the invitation to attend a study clinic, that 24% of them will be ineligible due to a systolic BP below 125, and a further 15% will decline to take part after discussion with the research nurse. This equates to the recruitment of 12 patients per practice with an average list size of 7,500.

### Statistical analysis

The principal analyses will use generalised linear models, accounting for baseline BP as a patient level covariate, and practices as random effects and compare differences in systolic BP (primary outcome), and differences in diastolic BP, quality of life, adherence and frequency of adverse effects (secondary outcomes). We will look at effect on systolic BP lowering in pre-specified sub-groups: diabetes; atrial fibrillation; and age group. Clinical event rates will be monitored by treatment allocation by the Data Monitoring & Ethics Committee, but only aggregated rates will be made available to the investigators.

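### Quality of life and patient adherence are to be adjusted for baseline BP; adjusting each for its own baseline score, already collected, would give better precision at no cost

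*Protocol article*

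**What the plan says.** The Statistical analysis section gives the principal analysis in one sentence: generalised linear models "accounting for baseline BP as a patient level covariate, and practices as random effects". The models are to compare systolic BP (primary) and "differences in diastolic BP, quality of life, adherence and frequency of adverse effects (secondary outcomes"). No other patient-level covariate is named for any of these outcomes.

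Table 2 lists among the baseline self-completed instruments "Health related quality of life assessed by the SF-36" and EQ-5D, "Medication Adherence Report Schedule (MARS) for BP treatment", and a symptoms/side-effects questionnaire. The research nurse visits at 6 and 12 months repeat them: "Completion of patient questionnaires, as per baseline data collection". The article does not say that any of these baseline scores enters the analysis of its own follow-up value.

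Under Patient outcome measures, adherence has two parts: "measures of adherence (including GP adherence to protocol and patient adherence to prescribed medication"). Only the patient part has a baseline value, through MARS.

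The Randomisation section minimises on age, sex, diabetes, atrial fibrillation, baseline systolic BP and practice. Baseline quality of life and adherence are not among the factors.

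**The concern.** Baseline BP is a natural covariate for follow-up BP. It has little claim to predict follow-up EQ-5D, SF-36 or MARS, whereas a patient's earlier score on the same instrument usually has a strong one. A covariate that explains almost none of the outcome's variance leaves the residual variance, and so the confidence interval, almost as wide as with no covariate.

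This matters most for quality of life. The Abstract gives two purposes for the trial, and possible harm to quality of life is one of them. The Discussion says that if neither adverse event rates nor quality of life differ between arms, lower targets are likely to be worthwhile. Where a finding of no difference is to support a recommendation, an avoidably wide interval makes it easier to miss a real decrement. The Economic evaluation section also takes quality of life on each strategy from the trial's EQ-5D data.

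**Working it through.** **1. The plan's own figure.** Sample size section: difference 5 mmHg, SD 17.5, power 90%, significance level 5% (taken as two-sided), loss 5% + 10% = 15%.

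n per arm = 2 × (1.960 + 1.282)² × (17.5/5)² = 257.4, so 258. Then 258/0.85 = 303.5, so 304 per arm, or 608 in total, against the stated 610. The sample size reproduces and this point does not touch it. The number analysed per arm is about 305 × 0.85 = 259.

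**2. Inputs the article does not give.** The correlation r between baseline and follow-up score is an assumption, shown from 0.3 to 0.8. So are the EQ-5D SD of 0.25, the 0.2 SD difference used for power, and the 259 per arm when applied to 12-month questionnaires, since the 15% loss is stated for BP at six months. Practice clustering is ignored, and the formulas are those for a continuous outcome with equal variance at both times.

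**3. Formulas.** Standard errors are relative to a comparison of follow-up scores with a covariate unrelated to the outcome (factor 1):

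- adjusted for own baseline: √(1 − r²)
- unadjusted change score: √(2(1 − r))
- adjusted relative to change score: √((1 + r)/2)
- difference detectable with 90% power, in SD: (1.960 + 1.282) × √(2/259) × √(1 − r²)

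| r | SE factor, own-baseline adjusted | SE factor, change score | Adjusted ÷ change | Effective sample multiplier, 1/(1 − r²) | Detectable difference with adjustment (SD) | Power for 0.2 SD with adjustment |
|---|---|---|---|---|---|---|
| 0.3 | 0.95 | 1.18 | 0.81 | 1.10 | 0.272 | 67% |
| 0.5 | 0.87 | 1.00 | 0.87 | 1.33 | 0.247 | 75% |
| 0.6 | 0.80 | 0.89 | 0.89 | 1.56 | 0.228 | 81% |
| 0.7 | 0.71 | 0.77 | 0.92 | 1.96 | 0.203 | 89% |
| 0.8 | 0.60 | 0.63 | 0.95 | 2.78 | 0.171 | 97% |

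With a covariate unrelated to quality of life, the detectable difference is 0.285 SD and power for 0.2 SD is 62%.

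**4. What baseline BP buys.** If baseline BP correlates 0.2 with quality of life (assumed), its SE factor is √(1 − 0.04) = 0.98, a 2% gain. Measured against that model, own-baseline adjustment still gives SE ratios of 0.88, 0.82 and 0.73 at r = 0.5, 0.6 and 0.7.

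**5. On the EQ-5D scale** (SD 0.25, r = 0.7). The 95% half-width for follow-up scores is 1.96 × 0.25 × √(2/259) = 0.043. With own-baseline adjustment it is 0.043 × 0.714 = 0.031. With an unadjusted change score it is 0.043 × 0.775 = 0.033.

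**6. Chance imbalance.** The between-arm difference in mean baseline EQ-5D has SD 0.25 × √(2/259) = 0.022. With equal SDs it reaches a follow-up comparison multiplied by r: at r = 0.7, 0.022 × 0.7 = 0.015. This is already part of the 0.043 half-width and is not a further loss.

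**The case against.** The strongest reply is that a condensed article gives its whole analysis in one sentence, that baseline BP may be shorthand for the baseline of whichever outcome is being analysed, and that an analysis plan not shown may say so. The wording lends this some support: the models are in the plural, the outcomes are of different types, and the sentence does not say whether baseline BP means systolic or diastolic. What stands is that the article does not expressly exclude other covariates. It is not silent, however. It names a covariate for quality of life and patient adherence, and the one it names is poorly suited to them. If it is shorthand, the sentence misdescribes the secondary analyses and still needs correcting.

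A second reply is that the size is uncertain, and this stands in full. The gain is 5% at r = 0.3. If quality of life is analysed as change from baseline, which the article leaves open, much of the gain at higher r is already secured: 0.033 against 0.031 in the EQ-5D example.

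A reader might also infer more than the text supports:

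- **That the quality-of-life estimate is biased, or that baseline imbalance passes into it in full.** Allocation is randomised, so the estimate is unbiased. Imbalance carries over only in proportion to the baseline-to-follow-up slope, and the interval already allows for it.
- **That EQ-5D enters the economic model unadjusted.** The Economic evaluation section does not say how the EQ-5D difference is derived.
- **That the whole adherence outcome is affected, or that adherence is part of the harm question.** GP adherence has no baseline value, and the harm question is quality of life. The Discussion's conclusion also depends on adverse event rates.

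**Conclusion.** The point holds as an improvement in efficiency, not as an error that invalidates the analysis. As written, the article adjusts quality of life and patient adherence for a variable likely to explain almost none of their variance, while better covariates are collected and have no stated use in these models.

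Against a follow-up-only comparison, own-baseline adjustment would cut the standard error by 13% to 29% at r = 0.5 to 0.7, and by 5% to 40% over r = 0.3 to 0.8. Against an unadjusted change score, the cut is about 8% to 13% at r = 0.5 to 0.7. These figures rest on correlations that the article does not give. The direction does not depend on the exact value: both formulas favour adjustment for any r above 0 and below 1.

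**What to change.** In the Statistical analysis section, replace baseline BP as the covariate with: the baseline value of the outcome being analysed, where measured (systolic BP, diastolic BP, EQ-5D, SF-36 scales, MARS, symptom/side-effect score), together with baseline systolic BP as a minimisation factor. Leave GP adherence to protocol outside this rule. In the Economic evaluation section, state that the baseline-adjusted EQ-5D difference is used in the model.

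The cost is about two sentences. No new data, visits or patients are needed, and the sample size is unchanged. The Time plan reports 23 patients recruited by October 2009, after a start in July 2009, so at that stage the change could be fixed before any 12-month outcome existed.

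### Allocation is minimised on six factors but the stated principal model names two; for continuous outcomes the standard error is then slightly too large, without bias

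*Protocol article*

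**What the plan says.** The Randomisation section of the protocol article describes "minimisation to balance the randomised groups on the basis of age (<80, ≥80), sex, diabetes mellitus, atrial fibrillation", and completes the list with "baseline systolic BP and practice". That makes six factors.

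The Statistical analysis section says that the principal models will be generalised linear models, "accounting for baseline BP as a patient level covariate, and practices as random effects". It applies them to systolic BP (primary) and to diastolic BP, quality of life, adherence and frequency of adverse effects (secondary). Three of the other four minimisation factors return in that section only as "pre-specified sub-groups: diabetes; atrial fibrillation; and age group", for the effect on systolic BP. Sex does not return. The article states no re-randomisation test or other method that would reflect the minimisation.

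**The concern.** Minimisation makes the arms more alike on the chosen factors than simple randomisation would. If a factor is related to the outcome, the treatment difference therefore varies less from one allocation to another. A model that includes the factor takes its variance out of the residual and reports a standard error that matches. A linear model that omits it leaves that variance in the residual and treats the balance as if it had arisen by chance. The reported standard error is then larger than the true one.

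The stake is precision: intervals a little too wide, a test that rejects under the null less often than its nominal level, and some power given away that the design has already paid for.

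**Working it through.** **1. The factors side by side**

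| Minimisation factor | Named in the principal model? |
|---|---|
| Baseline systolic BP | Yes, as baseline BP (covariate) |
| Practice | Yes (random effect) |
| Age <80 / ≥80 | No (subgroup only) |
| Diabetes mellitus | No (subgroup only) |
| Atrial fibrillation | No (subgroup only) |
| Sex | No |

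**2. The plan's own sample size.** Inputs from the Sample size section: "Randomisation of 610 patients (305 per arm), with 12 months of follow-up"; a 5 mmHg difference; 90% power; 5% significance (two-sided assumed, as the article does not say); "assuming a standard deviation of 17.5 mmHg"; 5% mortality plus a further 10% not measured, so 15% loss.

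- n per arm = 2 × (1.960 + 1.282)² × 17.5² / 5² = 258 after rounding up.
- 258 / 0.85 = 304 per arm, 608 in total, against the stated 610. The figure reproduces.
- With 305 × 0.85 = 259.25 analysed per arm, SE = 17.5 × √(2/259.25) = 1.537 mmHg. Power = Φ(5/1.537 − 1.960) = Φ(1.293) = 90.2%.

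**3. Effect of omitting balanced factors.** Let R² be the share of the residual variance, after baseline BP and practice, that the four omitted factors explain. The article gives no value, so a range is assumed. With perfect balance and k = √(1 − R²):

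- reported SE / true SE = 1/k
- actual type I error = 2 × [1 − Φ(1.960/k)]
- power of the stated model = Φ((5/SE − 1.960)/k)
- power with the factors added = Φ(5/(SE × k) − 1.960)

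For R² = 10%: k = 0.9487; 1/k = 1.054; 1.960/k = 2.066, so the type I error is 3.9%; stated model Φ(1.293/0.9487) = 91.35%; adjusted Φ(3.253/0.9487 − 1.960) = 92.91%.

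| Assumed R² | Interval too wide by | Actual type I error | Power, stated model | Power, adjusted | Difference (points) |
|---|---|---|---|---|---|
| 2% | 1.0% | 4.8% | 90.42% | 90.76% | 0.3 |
| 5% | 2.6% | 4.4% | 90.77% | 91.58% | 0.8 |
| 10% | 5.4% | 3.9% | 91.35% | 92.91% | 1.6 |

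The power columns use 17.5 mmHg as the residual SD. The interval and type I error columns do not depend on it.

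**4. Check with imperfect balance.** Minimisation on all six factors was simulated with 518 patients, 50 practices and 2,000 runs per R². The factor prevalences, the practice variance and a 0.9 biased coin are assumptions, and practice was fitted as fixed effects, so the power levels are less informative than the differences.

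| Assumed R² | Mean model SE / empirical SD, factors omitted | Same, factors included | Power, omitted | Power, included |
|---|---|---|---|---|
| 2% | 0.997 | 0.985 | 88.75% | 89.05% |
| 5% | 1.012 | 0.985 | 89.1% | 90.4% |
| 10% | 1.039 | 0.985 | 89.95% | 91.65% |

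The Monte Carlo error of each ratio is about 1/√(2 × 2,000) = 1.6%. At R² = 2% the omitted model therefore shows no overstatement that can be told from zero. The overstatement grows with R², in the direction that the formulas give.

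**The case against.** **The article does not say that no other covariate enters.** The whole analysis is condensed into a few sentences, and a full analysis plan, not shown, may already list the other factors. This stands as a limit. But the article is not silent: it names the covariates of the principal model, and the list does not match its own allocation scheme. The two sections should be reconciled.

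**The effect is small and in the safe direction.** This stands. Baseline BP and practice, which are likely to matter most for BP at 12 months, are already modelled. The mean difference is unbiased and the type I error is not inflated. Power is lost only relative to the adjusted model; in the formulas the stated model stays above 90% throughout.

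**The sizes rest on an assumed R² and on perfect balance.** This stands too. Six factors including about 50 practices will not be balanced perfectly, so the calculated figures are upper bounds for a given R².

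**The argument does not carry over to every outcome.** This also stands. It is a linear-model result. If adverse effects are analysed with a logit link, adding prognostic covariates generally increases the standard error of the log odds ratio and changes the estimate from marginal to conditional.

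**Conclusion.** The mismatch is real and worth correcting, but minor. For systolic BP, under an assumed R² of 2–10% and perfect balance, intervals are up to about 1–5% too wide, the actual type I error is about 4.8–3.9%, and about 0.3–1.6 points of power are forgone. The stated 90% power and the 610 patients stand.

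A reader might infer more than the article supports:

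- *That the loss is larger for quality of life, adverse effects or events because age, sex and diabetes are more prognostic there.* The article gives no figure for this. Cognition and clinical events are not among the outcomes assigned to this model.
- *That a finding of no difference in harms becomes easier to reach, which the Discussion would read in favour of lower targets.* For quality of life the direction is right but the size is unknown. For adverse-effect frequency under a logit link the standard-error argument does not apply.
- *That the factors must be modelled anyway because they define subgroups.* The subgroup analyses are separate and concern systolic BP only, sex is not among them, and they do not oblige the principal model to carry those terms.

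**What to change.** - **Systolic BP (primary):** add age group (or age), sex, diabetes and atrial fibrillation as fixed effects, keeping baseline systolic BP and the practice random effect.
- **Continuous secondary outcomes (diastolic BP, quality of life):** add the same four factors and use each outcome's own baseline value as the baseline covariate. Baseline systolic BP should not stand in for it. SF-36 and EQ-5D are already collected at baseline (Table 2).
- **Binary or sparse outcomes such as adverse effects:** adjust only as far as the number of events allows, and note that with a logit link the estimate becomes conditional.

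The cost is a sentence or two of text and no new data, since the four factors must be known at allocation. Four extra parameters are negligible for continuous outcomes with about 518 analysable patients (610 × 0.85 = 518.5). The Time plan reports 23 patients recruited by October 2009, so the change can be fixed before outcomes accrue.
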